**5.3. Procédure for premature STopping of the study or exclusion (stopping treatment + stopping follow-up)**

**5.3.1. Criteria and procedures for stopping treatment/medical device use and exclusion**

- *Premature stop criteria*

It is impossible to perform the evaluations, without and then with the spatula, due to patient behavior that involves their physical integrity (score of 5 on the Venham Scale).

- *Follow-up Methods for persons excluded from the study*

Patients with a score of 5 on the Venham Scale will be examined outside the study by using the following medical techniques:

- sedated by inhalation of an equimolar mixture of oxygen and nitrous oxide
- under sedation using Midazolam (intra-rectal or intravenous)
- Under general anesthesia if necessary.

**5.3.2. data collection and follow-up procedures**

The data will be collected in paper case report forms, from the source file of the

patient.

Patients only participate in one visit as part of the study. There is no follow-up planned.

**5.3.3. Procedure for of replacing people**

The number of subjects required is based on a 10% examination drop-out rate. Patients who have dropped out of the study will not be replaced.

.

**5.3.4 Follow-up procedure**

Not applicable.

**5.4. recruitment procedure**

The patients will be recruited:

- either in the Department of Odontology, as part of a preventive assessment or for oral healthcare (whatever it may be)
- or in the specialized institution on which the patient depends, as part of annual oral screening.

The inclusion period will be 33 months.

**6. medical device**

**6.1. medical device used**

*Figure 1: photo of the Oral Accessibility Spatula OAS*

[figure not shown]

## *Procedures employed when using the OAS.*

The OAS consists of a blade and a handle (see Appendices 1, 2 and 3). The shape of the blade facilitates its insertion into the oral cavity between the dental arches.

Rotating the handle makes it possible to exert sufficient force to cause the mouth to open.

The blade bears notches in which the maxillary and mandibular teeth can be wedged, thus wedging open the arches during the oral examination.

The spatula is made entirely of transparent polypropylene Bormed ™ RF830MO. This prevents trauma to the dental elements in case the patient bites down on the spatula.

The shape of the blade was carefully designed to prevent damage to the various tissues in the oral cavity.

The material is compatible with one sterilization according to current hospital standards: one sterilization with ionizing radiation from gamma rays (25 kGy).

The polypropylene Bormed ™ RF830MO can be sterilized by gamma radiation with one 25kGy dose. This mode of sterilization means the material will be sterile for 5 years if it is stored at ambient temperature. (See data sheet in Annex 5)

The users of this spatula during the clinical trial are dental surgeons who are accustomed to accessing the oral cavity.

The use of the OAS does not require, *a priori*, training of the investigators. However, instructions for its use have been produced (Annex 4) so that the technique for using the medical device is standardized. The users will be asked to carefully respect the the physical integrity of the person when using the spatula to access their oral cavity.

During the clinical trial, the OAS will be sterilized according to current hospital standards and packaged in individual sterile double packaging. They all come from the same manufacturing batch to ensure that they are completely identical. Each spatula will be disposed of after use and destroyed like any medical waste.

**6.2. Description of any medication, medical device (other than the experimental medication/medical device) that will be used for the research needs**

Not applicable

**6.3 Médications and treatments that are authorized and prohibited during the study**

- No medical device (other than the OAS) will be used to help open the oral cavity during the study.
- No sedative medication will be used outside the current treatments.

**6.4. Méthod for monitoring compliance**

The OAS is not a therapeutic device, rather, it is a device that provides technical assistance during preventive or curative management. Each patient only participates in one visit. Therefore, there will be no monitoring of patient compliance.

**7. EVALUATION OF EFFICACY**

## 7.1. Description of the efficacy variables

The data that will be collected to evaluate the effectiveness of the OAS are described in section 4.4.1

## 7.2. Planned methods and schedule for measuring, collecting and analyzing theefficacy variables.

The methods and schedule for measuring, collecting and analyzing these variables are described in section 4.5.

For all patients, effectiveness will be measured at the single study visit.

**8. Evaluation OF SAFETY:**

**8.1. Description of the safety variables**

The data collected as part of patient monitoring are described in section 4.4.2.

**8.2. Planned methods and schedule for measuring, collecting and analyzing the safety variables**

Each patient is evaluated once in this study. The safety variables will be identified during this visit.

**8.3 Procédures for the registration and notification of adverse events**

**8.3.1 Definitions**

An **adverse event** is any untoward medical occurrence in a person who participates in biomedical research, regardless of whether this event is causally linked to the research or the study device.

An **adverse reaction** to a medical device is any adverse and unwanted reaction to the medical device or any incident that could have caused this reaction if an action had not been carried out, in a person who participates in research or in the user of the medical device; or any reaction that relates to failure of the medical device that is harmful to the health of the study subject.

A **serious adverse event (SAE) or serious adverse reaction** is an event or a reaction that is life-threatening; may have contributed to the death, hospitalization, or prolongation of hospitalization of the patient; contributed to incapacitation or a significant or long-lasting disability; resulted in a birth defect or congenital malformation; or any event deemed significant by the investigator.

**The list of expected adverse events** in the study is based on the reference document.

An SAE is considered to be a suspected unexpected serious adverse reaction (SUSAR) when it is not on this list.

**A new fact** can be: unexpected frequency of an expected SAE, an SAE that relates to the test procedure, insufficient efficacy in life-threatening diseases, non-clinical data.

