**8.3.2 Reference document for defining SAEs**

There is no reference document for the experimental medical device under study, since it is a new medical device.

An investigator brochure has been produced by [name], the inventor of the spatula.

The expected events are those that are frequently encountered when using intraoral rubber mouth props, metal gags, or spinning top-shaped devices.

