**8.3.3 List of expected adverse reactions**

Adverse reactions that relate to the use of the experimental medical device are currently not known because it is a new medical device.

The expected adverse events in the list for evaluating spatula-related incidents are:

- labial injuries
- gingival injuries
- cheek injuries
- lingual injuries
- dental fracture
- dental luxation
- dental expulsion
- nausea/vomiting
- pain
- joint complications
- others

Expected SAEs are inhalation or ingestion of a tooth or a tooth fragment that requires hospitalization.

Inhalation or ingestion of a tooth or tooth fragment may occur as a result of dental dislocation or fracture, events occurring on a tooth that moved before the examination was performed.

A maximum of 1 to 2 OAS-related SAEs is expected for all patients included in the study.

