**8.3.4 Notification of SAEs or new facts**

As soon as an investigator becomes aware of an SAE or a new fact, he/she will notify the sponsor without delay by faxing the SAE declaration form (Annex 7).

- If it is an suspected unexpected serious adverse reaction (SUSAR), the sponsor will contact the investigator to write an initial report that will be sent to ANSM, the ethics committee, and the coordinating investigator within 7 days (if the SUSAR is life-threatening or the patient has died) or 15 days (in other cases).

If the event is not resolved by the date the fax is sent, the investigator is required to send an supplementary report (within 8 days in the event of death or a life-threatening SUSAR; within 15 days in other cases) to document progress in the case or to update missing data.

- If it is an SAE that is linked to the use of the experimental medical device, the declaration will be sent to the ANSM as described above and to the ethics committee every quarter.
- If it is a new fact, the sponsor will declare it to the ANSM and the ethics committee within a maximum of 15 days; additional information can be provided within an additional 15 days.
- If it is an expected SAE, it will be recorded by the sponsor and reported in the annual safety reports.

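### The catch-all *others* in the expected-event list empties the SUSAR definition on its literal reading, and the SAE reporting routes in section 8.3.4 conflict

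*Protocol*

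**What the plan says.** Four consecutive protocol sections decide how a serious event is classified and reported.

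- **8.3.1 Definitions.** The list of expected events "in the study is based on the reference document". The test for a SUSAR follows: "An SAE is considered to be a suspected unexpected serious adverse reaction (SUSAR) when it is not on this list".
- **8.3.2 Reference document.** "There is no reference document for the experimental medical device under study, since it is a new medical device". The section then mentions an investigator brochure, and says the expected events are those often met with existing mouth props, gags and spinning-top devices.
- **8.3.3 List of expected adverse reactions.** This opens by saying that reactions to the device are not yet known. It continues: "The expected adverse events in the list for evaluating spatula-related incidents are", followed by ten named injuries or symptoms and the entry *others*. A separate sentence then reads: "Expected SAEs are inhalation or ingestion of a tooth or a tooth fragment that requires hospitalization". The section forecasts at most 1 to 2 OAS-related SAEs over the whole study.
- **8.3.4 Notification.** Investigators inform the sponsor of any SAE or new fact without delay. Onward reporting has four bullets: SUSARs, device-linked SAEs ("If it is an SAE that is linked to the use of the experimental medical device"), new facts, and expected SAEs ("If it is an expected SAE, it will be recorded by the sponsor and reported in the annual safety reports").

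**The concern.** The 11 entries in 8.3.3 are the same 11 yes/no items that the section after 4.4.1 sets out for recording OAS-related adverse events. *Others* is sensible on a recording form, where it makes sure nothing goes unrecorded. In a list that defines what is expected, it covers every event, so nothing can be absent from the list.

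At stake is how soon bodies outside the trial learn of a serious event. The device is class I without CE marking (11.1), and it is used in minors and legally protected adults (section 5). There is no independent monitoring committee and no event-evaluation committee (8.5.2, 8.5.3), and no statistical stopping criterion (9.4). The sponsor's reports to the authority and the ethics committee are therefore a main outside safeguard, and their trigger should be clear.

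**Working it through.** The protocol gives no figure to reproduce here. The check sets the sections side by side.

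**Step 1: which list does the SUSAR test use?** Section 8.3.1 speaks of the list of expected adverse events. Section 8.3.3 offers two candidates: the 11-entry list (10 named + 1 catch-all = 11), which uses the same term, and the closed sentence on expected SAEs, which concerns the same class of event as the test. The protocol does not choose between them. The choice changes the answer:

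| SAE | Against the 11-entry list | Against the closed sentence |
| --- | --- | --- |
| Tooth or fragment inhaled, patient hospitalized | Expected, but only through *others* | Expected |
| Joint complication, patient hospitalized | Expected (named) | Unexpected |
| Serious event of a kind named in neither place | Expected through *others* | Unexpected |

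Under the first reading no row can be a SUSAR. Under the second, two of the three are unexpected. The first row also shows that deleting *others* is not enough: inhalation is not one of the ten named entries, so it would then be off the list in 8.3.1 terms while 8.3.3 calls it expected.

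**Step 2: what is the source of the list?** Section 8.3.1 points to a reference document, and 8.3.2 denies that one exists. The brochure is mentioned but not given that role.

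**Step 3: which route applies to an SAE that is both OAS-linked and expected?** An example is hospitalization after a tooth fragment is inhaled during use of the OAS.

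| Bullet in 8.3.4 | ANSM | Ethics committee | Does it apply? |
| --- | --- | --- | --- |
| SUSAR | 7 or 15 days | 7 or 15 days | No, the event is expected |
| Device-linked SAE | In the manner already described; the only ANSM deadlines given before it are 7 or 15 days | Quarterly | Yes; no condition on expectedness |
| New fact | At most 15 days | At most 15 days | Arguably; 8.3.1 counts an SAE related to the test procedure as a new fact |
| Expected SAE | Annual report | Annual report | Yes |

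The ethics committee could thus be told in 15 days, at the quarter or at the year, and nothing ranks the bullets. (Recipients of the annual report are taken from 8.6.)

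**Step 4: what is lost on the literal reading?** For a device-linked SAE of an unforeseen kind, the ANSM route remains through the device-linked bullet. What disappears is the SUSAR report to the ethics committee and coordinating investigator in 7 or 15 days. The form in Annex 7 also lets the investigator answer that the cause cannot be determined. Such an SAE does not clearly fall under the device-linked bullet, so the literal reading leaves it the annual route and possibly the new-fact route.

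**Step 5: causality.** The sentence in 8.3.1 has no condition on a link to the device. Under the closed-sentence reading, an unrelated SAE would then count as a SUSAR.

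**Forecast.** In 200 patients, the anticipated OAS-related SAEs are at most 1/200 = 0.5% to 2/200 = 1%. This shows how rarely the conflict in Step 3 is expected to arise. It does not count events that would be misclassified.

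**The case against.** The case for leaving the text alone is that a sensible sponsor would read it correctly. *Others* is recognisably a form category. The closed sentence on expected SAEs is a natural comparator for a test about SAEs. The Annex 7 form has the sponsor mark each SAE as expected or unexpected, so the protocol plainly foresees unexpected ones. Section 8.3.2 does state a basis for expectedness, namely experience with comparable devices. The steering committee also follows adverse events (8.5.1).

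Much of this stands, and it limits the point. A reader might infer that expedited reporting can never be triggered, or that expectedness alone decides between days and a year. The documents do not support either inference. The device-linked and new-fact bullets do not require SUSAR status, and every SAE goes to the sponsor at once. Nor is it settled that no SAE can be a SUSAR, since that depends on which of the two lists in 8.3.3 governs.

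The objection does not remove the contradiction. The sponsor must tick one box in Annex 7, and for a serious joint complication the two readings give opposite answers. The steering committee consists of the initiating clinician, the biostatistician and sponsor representatives, so it does not replace outside reporting. The brochure was not available, so whether it could serve as the reference cannot be judged.

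**Conclusion.** The point holds as an internal contradiction in safety reporting that should be corrected. It has three parts:

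- The SUSAR definition is empty if the 11-entry list governs, and workable if the closed sentence governs. The protocol does not say which does.
- The list is attributed to a document that the next section says does not exist.
- An SAE that is both device-linked and expected has two applicable routes and arguably a third, with deadlines to the ethics committee from 15 days to a year.

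A delay of up to 12 months for a serious device reaction is a tempting figure. It arises only if the annual bullet is followed and the other applicable bullets are ignored; the text permits that choice but does not require it. The first part rests on reading the list in 8.3.1 as the one printed in 8.3.3. The second and third do not depend on that reading.

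**What to change.** 1. In 8.3.3, remove *others* from the list that defines expectedness, and keep it as a recording category on the case report form.
2. State which list governs the expectedness of SAEs. This must accompany the first change, because inhalation or ingestion of a tooth is not among the ten named entries.
3. Name one source for that list, in the same words in 8.3.1 and 8.3.2.
4. Say in 8.3.1 whether a suspected link to the device is part of the SUSAR definition.
5. Reconcile the bullets of 8.3.4 so that each class of SAE has one route and one deadline for each recipient. Which deadline applies is for the sponsor to settle against its reporting obligations.

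The cost is wording in 8.3.1 to 8.3.4 and possibly a few more expedited reports. No endpoint, sample size or study procedure changes.

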**8.3.2 Reference document for defining SAEs**

There is no reference document for the experimental medical device under study, since it is a new medical device.

An investigator brochure has been produced by [name], the inventor of the spatula.

The expected events are those that are frequently encountered when using intraoral rubber mouth props, metal gags, or spinning top-shaped devices.

**8.3.3 List of expected adverse reactions**

Adverse reactions that relate to the use of the experimental medical device are currently not known because it is a new medical device.

The expected adverse events in the list for evaluating spatula-related incidents are:

- labial injuries
- gingival injuries
- cheek injuries
- lingual injuries
- dental fracture
- dental luxation
- dental expulsion
- nausea/vomiting
- pain
- joint complications
- others

Expected SAEs are inhalation or ingestion of a tooth or a tooth fragment that requires hospitalization.

Inhalation or ingestion of a tooth or tooth fragment may occur as a result of dental dislocation or fracture, events occurring on a tooth that moved before the examination was performed.

A maximum of 1 to 2 OAS-related SAEs is expected for all patients included in the study.

**8.3.4 Notification of SAEs or new facts**

As soon as an investigator becomes aware of an SAE or a new fact, he/she will notify the sponsor without delay by faxing the SAE declaration form (Annex 7).

- If it is an suspected unexpected serious adverse reaction (SUSAR), the sponsor will contact the investigator to write an initial report that will be sent to ANSM, the ethics committee, and the coordinating investigator within 7 days (if the SUSAR is life-threatening or the patient has died) or 15 days (in other cases).

If the event is not resolved by the date the fax is sent, the investigator is required to send an supplementary report (within 8 days in the event of death or a life-threatening SUSAR; within 15 days in other cases) to document progress in the case or to update missing data.

- If it is an SAE that is linked to the use of the experimental medical device, the declaration will be sent to the ANSM as described above and to the ethics committee every quarter.
- If it is a new fact, the sponsor will declare it to the ANSM and the ethics committee within a maximum of 15 days; additional information can be provided within an additional 15 days.
- If it is an expected SAE, it will be recorded by the sponsor and reported in the annual safety reports.

**8.3.5 Notification of non-serious adverse reactions**

They will be described briefly by the investigator in the case report form in the section dedicated to adverse events.

**8.4. Procedures and duration of follow-up of persons with adverse events**

When a serious adverse event persists, even after the end of the study, the investigator will follow the patient until the event is considered resolved. The follow-up data will be sent to the sponsor.

**8.5. Committees specific to the research (varies depending on the protocol)**

**8.5.1 Steering committee**

It will consist of the initiating clinician of the project, the biostatistician in charge of the project and the representatives of the sponsor.

It will define the general organization and conduct of the research and will coordinate the information.

It will initially determine the methodology; will decide what do do in unforseen cases during the course of the research; and will monitor the progress of the research, particularly regarding patient tolerance and adverse events.

### 8.5.2 Independent monitoring committee

The nature of this study does not justify the establishment of an independent monitoring committee.

### 8.5.3 Independent committee for evaluating critical events

The nature of this study does not justify the establishment of an independent committee that evaluates critical events.

**8.6 Safety reports**

- Annual safety reports: the sponsor drafts the annual safety reports and sends them to the ANSM, the ethics committee, and the coordinating investigator. The coordinating investigator will send the sponsor all of the data needed to draft these reports.
- Final report: it is written by the sponsor and the coordinating investigator within a one year of the end of the study. All investigators will be informed of the results of the study.

A summary is sent to the ANSM by the sponsor.

**9. StatistiCS**

**9.1. description of the planned statistical méthods, including the schedule for planned intermediate analyses**

The main analysis will consist of

1. Describing the sample to assess the necessity and feasibility of using the OAS,

2. Checking the inclusion criteria and the representativeness of the final sample,

3. Comparing the examinations with and without the OAS in terms of the frequency of patients whose oral accessibility score was at least 8 by using a McNemar test, and the average oral accessibility scores by using Student's Paired *t-*test. The data will also be examined for possible center and investigator effects.

4. Evaluate the safety of the OAS by quantifying and describing the observed adverse events.

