**16. List of annexes**

**17. BIBLIOGRAPHIC REFERENCES**

**1.** PROTOCOL SUMMARY

| Title | *OAS: Evaluation of the effectivess and safety of an innovative medical device designed to enhance the oral accessibility of people with a handicap who have behavioral disorders: the Oral Accessibilty Spatula (OAS)* |
| --- | --- |
| Sponsor | *CHR METZ THIONVILLE* |
| Investigator Coordinator | *[name] [name]*  *Department of Odontology*  *CHR METZ-THIONVILLE – Bel Air Hospital*  *[name]*  *[contact] / Email: [contact]* |
| protocol version | *V4.0 produced 11/08/2017* |
| Justification/context | *It is sometimes difficult, even impossible, to access the oral cavity of people with a behavioral handicap. This is because of their defensive reflexes, where they spontaneously limit the amplitude of the mouth opening or keep their mouth open for very short periods only.*    *The currently available means of keeping the oral cavity open are often unsuitable for these patients and alternative devices have not been described in the literature.*  *This problem makes it difficult to perform preventive oral examinations or provide these patients with oral healthcare.* |
| Main Objective | *Evaluation of oral accessibility during the initial oral examination without and then with the oral accessibility spatula (OAS).* |
| Secondary Objectives | *Evaluation of the safety of the OAS*  *Evaluation of the tolerability of the examination without and with the OAS*  *Evaluation of operator comfort when using the OAS* |
| Primary Endpoint | *Visibility and probe-ability of the three tooth sectors (incisors/canines, premolars, and molars) during the examinations without and with the OAS, as indicated by using an Oral Accessibility Score (this score ranges from 0 = no accessibility to 12 = total accessibility)* |
| Secondary Endpoints | *Identification of adverse events and their frequency.*  *Venham Behavioral Rating Scale*  *Numerical scale measuring operator satisfaction* |
| Méthodology / Study design | *Prospective interventional study, multicenter, open-label*  *Only one visit is planned per patient.* |

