| Duration of Research | *Only one visit is planned per patient.*  *The total duration of the study therefore corresponds to the recruitment period, which is 33 months.*  *Expected start of the study: March 2016*  *End of recruitment: December 2018*  *End of the study: June 2019* |
| statistical analysis | *The principal analysis will be comparison of the oral accessibility scores during the examination with and without the OAS. Each subject will serve as their own control and the examinations will always be conducted first without the OAS and then with the OAS by the same dental surgeon* |
| Expected results | *The expected result is that the OAS will provide a better quality oral examination without risk to the patient. It is expected that dentists will then be provided with the OAS to improve the therapeutic indications for the use of this tool and the quality of interventions. Thereafter, the OAS will be provided to parents, carers, and nursing staff to facilitate preventive oral healthcare in people with disabilities or dependency.*  ***The expected benefits are therefore as follows:***   - *early detection of oral diseases* - *increased effectiveness of the care provided* - *reduction of the indications for care under general anesthesia* - *facilitating toothbrushing, thereby significantly improving the oral hygiene of these people* - *increasing the prevention of oral diseases by making this spatula available to parents, carers, companions, and healthcare professionals.* |

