**9.2. Number of people to include in the research and the statistical justification**

Without the OAS, 20% of the patients will have an oral accessibility score of at least 8.

The protocol hypothesizes that the use of the OAS will improves this frequency by 20% (*i.e*. 40% of patients will have a score of at least 8). To validate this hypothesis with an α of 5% and a power of 90%, a total of 140 patients is needed. When potential center-related and investigator-related effects and a study drop out rate of 10% are taken into account, the patient number rises to 200.

**A feasibility study** was conducted in the Department of Odontology of the CHR METZ-THIONVILLE over a period of 12 months (January to December 2009). During this period, 104 patients meeting the inclusion criteria of our study were aided by the Department of Odontology, which confirms the feasibility of the recruitment target that was set.

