**9.3. degrée of planned statistical significance**

The α is fixed at 5%

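### Section 9.1 puts two tests of the accessibility score in the main analysis under a single 5% level, with no rule for which one decides

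*Protocol*

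**What the plan says.** **Section 9.1.** The list of analyses opens "The main analysis will consist of". Its third item compares the examinations with and without the spatula "in terms of the frequency of patients whose oral accessibility score was at least 8 by using a McNemar test" and, in the same sentence, "the average oral accessibility scores by using Student's Paired" t-test. The two are simply joined, "by using a McNemar test, and the average oral accessibility scores by using" the paired test, and neither is called primary, secondary or supportive.

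**Section 9.3.** "The α is fixed at 5" per cent. There is no split, order or requirement that both tests succeed, and sidedness is not stated.

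**Section 1 (summary), Primary Endpoint row.** Accessibility is measured "as indicated by using an Oral Accessibility Score (this score ranges from 0 = no accessibility to 12 = total accessibility"; no cut-off is given. Section 4.1 describes the primary assessment in the same way.

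**Section 1, statistical analysis row.** "The principal analysis will be comparison of the oral accessibility scores during the examination with and without the OAS". This names neither the share at 8 or more nor the mean.

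**Section 9.2, and the Number of Patients row of the summary.** The hypothesis is a rise from 20% without the spatula to the point where "40% of patients will have a score of at least 8". The 5% α, the 90% power and the 140 patients (200 after allowances) are attached to that hypothesis. No expected difference or power is given for the mean score.

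**The concern.** The share at 8 or more and the mean score are two summaries of one endpoint, and they can give different answers. If most patients moved from a score of 2 to 5, the mean would rise by up to 3 points while the share at 8 or more would not move. Conversely, a shift of a few patients from 7 to 8 changes the share and hardly changes the mean.

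With no deciding test named, the result that carries the trial could be picked after both are known. Taken that way, the error rate is that of two chances at 5%, not one, and the stated 90% power describes only one of them. A reader of the final report could not tell from the protocol whether a significant mean with a non-significant share, or the reverse, counts as success.

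**Working it through.** **1. Which version do the passages support?**

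| Place in the protocol | Version of the endpoint |
| --- | --- |
| Summary, Primary Endpoint row; section 4.1 | 0-12 score, no cut-off |
| Summary, statistical analysis row | comparison of scores, version not named |
| Summary, Number of Patients row; section 9.2 | share with a score of at least 8 |
| Section 9.1, item 3 | both, without rank |
| Section 9.3 | one 5%, not assigned to a test |

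The endpoint wording points to the score and the sizing points to the share. No passage reconciles them.

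**2. The plan's own figure.** For a McNemar test with discordant fraction ψ and difference d = 0.40 − 0.20 = 0.20, n = [1.960·√ψ + 1.282·√(ψ − d²)]² / d² at two-sided 5% and 90% power.
- Independent examinations: ψ = 0.20 × 0.60 + 0.80 × 0.40 = 0.44. Then n = (1.300 + 0.811)² / 0.04 ≈ 111.4, so 112 (117 with continuity correction).
- ψ = 0.55: n = (1.454 + 0.915)² / 0.04 ≈ 140.3, so 141.

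The stated 140 therefore needs a discordant fraction of about 0.55, which the protocol does not give. This does not affect the error-rate question. It confirms only that the sizing concerns the share, not the mean.

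**3. Error if either test may carry the claim.**
- Upper reference, independent tests: 1 − 0.95² = 9.75%.
- Two correlated normal statistics, P(|Z₁| > 1.96 or |Z₂| > 1.96): 9.1% at correlation 0.5, 8.3% at 0.7, 7.8% at 0.8, 7.0% at 0.9.

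The correlation is not in the protocol, so I simulated trials with no spatula effect. Paired 0-12 scores came from the same distribution at both examinations. There were 140 or 180 pairs (200 × 0.9 = 180), 16% to 20% of scores at 8 or more, within-patient latent correlation from 0 to 0.9, and 20,000 trials per setting, with two-sided 5% tests.

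| Quantity | Range over settings |
| --- | --- |
| Correlation of the two statistics | 0.44 to 0.74 |
| Paired t-test alone | 4.6% to 5.2% |
| McNemar alone, uncorrected | 4.7% to 5.6% |
| McNemar alone, continuity-corrected or exact | 2.6% to 3.6% |
| Either significant, uncorrected McNemar | 7.9% to 9.6% |
| Either significant, corrected or exact McNemar | 6.7% to 7.7% |
| Either significant in favour of the spatula, uncorrected | 3.9% to 4.7% (nominal 2.5%) |

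A second set of runs, with 22% at 8 or more, gave 7.5% to 9.5% (uncorrected) and 6.5% to 8.0% (exact). A third, with 26% to 31% at 8 or more and 180 pairs, gave 7.8% to 8.9%. Taken together the range is 6.5% to 9.6%.

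**4. Error under other rules.** If both tests had to be significant, the error could not exceed that of either test, so at most 5%. With one named primary test, or a fixed order, it is 5%.

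**5. Cost of splitting α instead.** At 2.5% for each test, with ψ = 0.55: n = (2.241 × √0.55 + 1.282 × √0.51)² / 0.04 = (1.662 + 0.915)² / 0.04 ≈ 166.1, so 167 instead of 141. That is below 180, but it uses part of the margin that section 9.2 sets aside, without quantifying it, for center and investigator effects.

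**The case against.** The best counter-argument is that sections 9.1 to 9.3, read together, already imply a deciding test. Section 9.2 states one hypothesis and ties α and power to it, 9.1 names that comparison first, and no hypothesis is given for the mean. The main-analysis list also covers describing the sample, checking inclusion criteria and describing adverse events, so being on it does not make a test confirmatory. This stands in part. A reader might infer that the 5% belongs to neither claim, but 9.2 attaches it to the share at 8 or more. What it does not answer is that the endpoint and principal analysis in the summary point to the score itself, and that 9.1 gives the two tests equal rank.

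It is also fair that no passage says one significant test is enough. An either-test claim is a possibility left open, not a rule in the protocol, so an error of about 8% should not be read as the trial's actual error rate.

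Ranking of tests is often left to a statistical analysis plan, which is not at hand. Such a plan might settle the choice, but the protocol's endpoint, sizing and main-analysis wording would still need to be brought into line.

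A reader might also think the open-label design makes this worse. Choosing between two tests at analysis is equally possible in a blinded trial. The assessment and habituation biases conceded in section 4.3 are a separate matter.

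Finally, other remedies would control the error: the mean as primary, both required, or a split α. The choice below is the one that fits the existing sample size, not the only valid one.

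**Conclusion.** The point holds as an inconsistency within the protocol: two versions of the endpoint share the main analysis and one 5% level, the endpoint definition and the sample size favour different versions, and nothing says which decides.

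The size is conditional. If either test could carry the claim, the two-sided error is about 6.5% to 9.6%, and about half of that in favour of the spatula against a nominal 2.5%. This rests on two-sided testing, on a correlation between the tests that comes from an assumed score model, and on the McNemar version, which the protocol does not specify. Every setting tried was above 5%. The 90% power applies only to the share at 8 or more. The matter should be corrected, but it does not call the design or the number of patients into question.

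**What to change.** In section 9.1, name one primary analysis: the within-patient comparison, by McNemar test at two-sided 5%, of the share of patients with a score of at least 8. Make the mean score a secondary analysis, tested for confirmation only if the primary is significant and otherwise reported descriptively with its confidence interval. Bring the Primary Endpoint and statistical analysis rows of the summary into line, so that the cut-off appears where the endpoint is defined. Section 3.1 states an objective, not a test, and needs no change.

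The cost is wording only; the number of patients is unchanged. The downside is that the mean score alone can no longer carry the trial, so an improvement that stays below 8 would be described but not claimed as confirmed. If the sponsor regards the mean as the more meaningful measure, it could be named primary instead, but section 9.2 would then need an expected difference, a standard deviation and a power for it.
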